### Procedure

As part of the intake procedure of the mental health institute, routine outcome assessment (ROA) measurements are conducted in most departments of the institute, using an established online platform [21]. We will use this infrastructure, to reduce the burden to the participants and ensure data quality. Participants will be asked to complete questionnaires prior to the intake procedure (T0), 6 (T1), and 12 (T2) months later.

To screen for sleep disorders, patients fill out the Holland Sleep Disorders Questionnaire (HSDQ) [22, 23]. Patients who score above the cut-off score for any specific category of sleep disorders will be invited to participate in this study. After being informed about the study procedures, they will be asked for informed consent.

For both the experimental and control conditions, participants will continue their treatment as usual (TAU) throughout the study. After stratification for type of mental disorder, participants will be randomly assigned (using Sealed Envelope software) to either the experimental or control condition. In the experimental condition sleep intervention(s) (SI) will start immediately at T0 (TAU+SI-T0). In the control condition, the sleep intervention(s) will first start six months after inclusion, at T1 (TAU+SI-T1). This allows to test the effects of early interventions for sleep disorders on mental disorder symptoms, general functioning, sleep, and quality of life. Sleep interventions generally start with extensive diagnostic evaluation, followed by patient-targeted sleep treatment. For individuals scoring below the cut-off score for a sleep disorder on the HSDQ, participation is limited to filling out the questionnaires at T0. An exception to randomised allocation will be made for participants in the control condition whose HSDQ result or intake interview indicates a very severe sleep disorder, such as Narcolepsy. These participants will be immediately referred to a sleep centre, regardless of original randomization. These patients will be included in the prevalence estimate, but excluded from the analysis of the treatment effects. An overview is provided in Fig. 1.

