**Fig. 1 Fig1:**
[figure not shown]
Study procedure. Patients who score above the cut-off score for any type of sleep disorder on the Holland Sleep disorders Questionnaire (HSDQ+) will be invited for extensive diagnostic evaluation, followed by patient-targeted sleep treatment. Those participants will be randomly divided in one of two conditions: in TAU+SI-T0 sleep diagnosis and sleep intervention (SI) will start immediately (T0), in addition to the treatment as usual (TAU). In TAU+SI-T1 sleep diagnosis and SI will start after 6 months (T1). Questionnaires will be filled in at T0, T1 and T2 (after 12 months), measuring sleep, general functioning, specific mental disorder symptoms, and quality of life. For patients scoring below the cut-off score for a sleep disorder (HSDQ-), participation is limited to filling out the questionnaires at T0

This research project will be conducted in collaboration with a sleep centre for psychiatry. Anamnestic interviews, diagnostic assessments and sleep interventions will be provided by trained staff.

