#### Sleep

The HSDQ [22] is a 32-item self-assessment questionnaire for sleep disorders, based on the International Classification of Sleep disorders (ICSD-2) [24]. Each item consists of a self-description (i.e. “I have difficulty falling asleep”) and participants are instructed to respond on a 5-point Likert scale indicating if the stated item applies to them for the past 3 months (1= “not at all”, 2 = “usually not”, 3 = “sometimes”, 4 = “usually”, 5 = “completely”). This questionnaire is validated (Cronbach’s alpha (α) = .90) [22] and screens for the following categories of sleep disorders: Chronic insomnia (α = .92), parasomnia (α = .85), CRSD (α = .84), hypersomnia (α = .78), sleep-related movement disorders (i.e. restless legs syndrome (RLS)) (α = .81), and SRBD (i.e. obstructive sleep apnea (OSA)(α = .62)) [23]. The total score of the HSDQ distinguishes individuals with a clinically diagnosed sleep disorder from individuals without sleep complaints (area under the curve, *P*(A) = .95) and the diagnostic accuracy of the HSDQ is high (kappa = .80) [22]. In the present study, the HSDQ will be used for screening purposes and to assess sleep disorder prevalences. Mean scores will be calculated and the following cut-off criteria will be used: Sleep disorder > 2.02; chronic insomnia > 3.68; parasomnia > 2.42; CRSD > 3.42; hypersomnia > 2.9; sleep-related movement disorder > 2.7; SRBD > 2.87 [22]. For the analysis of sleep treatment effect on response of the clinical sleep disorder(s), the HSDQ total and subscale scores will be used as outcome variables.

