### Sample size calculations

Power analysis were performed using G*Power software [45]. Based on previous studies [18, 46], we aim at an effect size of 0.4 (Cohen’s d) for the outcome variables “quality of life”, “general functioning” and “mental disorder specific symptoms”. Power analysis based with an α of .05 and a power of .8, resulted in a required group size of 48 patients per diagnostic group (24 TAU+SI-T0 and 24 TAU+SI-T1). Due to limitations in recruitment capacity in less prevalent disorders, differences across both sexes will only be examined in the relatively high prevalent disorders: depression and PTSS. Power analysis with a 2 × 2 experimental group design (TAU+SI-T0 versus TAU+SI-T1; and males versus females) as between subject factors and the three time points as within subject factors suggests that with an α of .05 and a power of .8 a group size of 92 per group (46 TAU+SI-T0 and 46 TAU+SI-T1) would be sufficient. This analysis assumes an equal sex distribution. Overall, a total of 472 participants will be included in this study (overview provided in Table 2).

**Table 2 Tab2:** *Overview of targeted sample-sizes per diagnostic category*

Group	Prevalence (%)	Sec. analysis: yes/no	Required number per experimental group	Total required number per diagnostic subgroup	% of total population needed to include
**Depression**	17	Yes	46	92	15.0
**Bipolar disorder**	3	No	24	48	44.4
**Anxiety disorder**	10	No	24	48	13.3
**PTSD**	15	Yes	46	92	18.1
**ADHD/ADD**	9	No	24	48	14.7
**ASD**	4	No	24	48	33.1
**SSD**	5	No	24	48	26.7
**Personality disorder**	6	No	24	48	22.3
**Total**			**236**	**472**	

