### Statistical analyses

#### Data exploration/ missing data

Separate analyses will be performed for the different questionnaires, using SPSS (version 23) and R software. If data are not normally distributed, data transformations will be performed. A data management plan was generated using online software and can be found at DMPonline (https://dmponline.dcc.ac.uk/).

If a participant stops participation halfway the study or if a specific questionnaire is missing at a specific time point this will be dealt with as follows: if the last data point (T2) is missing, the participant will be included in the analysis for the prevalence and in any analysis focussed on de comparison between T0 and T1. For those participants that are missing a complete questionnaire at T1, but do have the T2 measurements, T1 will be treated as a missing data point and imputed using multiple imputation. If a participant is missing both the T1 and T2 data point, this participant will only be included in the prevalence analysis.

Because we make use of a delayed start for the sleep treatment in the TAU-SI-T1 group, there is a possibility that some participants in the TAU-SI-T1 control group score above the cut-off score for a sleep disorder on the HSDQ at T0, but below the cut-off score for a sleep disorder at T1. In this case, these participants will be informed about the change in their HSDQ score, and that they are no longer eligible for sleep disorder treatment, and thus excluded from the treatment part of the study. Another scenario is that a participant scores above a cut-off score of the HSDQ, but that the sleep disorder is not confirmed in the diagnostic evaluation. In this case, the participant will also be excluded from the treatment part of the study.

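### Post-randomisation exclusions remove improved controls only, and unconfirmed cases at a time that differs by arm; read as analysis exclusions, they favour early treatment

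*Protocol article*

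**What the plan says.** All places are in the Methods of the protocol article.

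- **Procedure.** After the screening HSDQ at T0 and stratification by mental disorder, "participants will be randomly assigned (using Sealed Envelope software) to either the experimental or control condition". Controls found to have a very severe sleep disorder are referred at once and left out of the treatment-effect analysis.
- **Data exploration/ missing data, rule 1.** Control participants above the HSDQ cut-off at T0 but below it at T1 are told that "they are no longer eligible for sleep disorder treatment, and thus excluded from the treatment part of the study".
- **Same section, rule 2.** For a positive HSDQ that the diagnostic evaluation does not confirm: "In this case, the participant will also be excluded from the treatment part of the study".
- **Fig. 1 legend.** Diagnosis starts immediately in the early arm. For controls: "In TAU+SI-T1 sleep diagnosis and SI will start after 6 months (T1").
- **Sleep measures.** For the treatment effect, "the HSDQ total and subscale scores will be used as outcome variables".
- **Effect of sleep disorder treatment.** The arms are compared over T0, T1 and T2 with a separate linear mixed model per outcome, among participants who have a sleep disorder. Quality of life and general symptoms are analysed in the whole sample, disorder-specific symptoms within the eight diagnostic groups.

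**The concern.** Both rules act after randomisation, and neither acts alike in the two arms.

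Rule 1 names controls only. Someone in the early arm who is below the cut-off at T1 stays and counts as improved; a control with the same score leaves. The score that triggers removal is an outcome at an analysed time point. Because entry required a high score, some controls will fall below the cut-off through regression to the mean or through usual care alone, and the article itself foresees such cases.

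Rule 2 applies to both arms, but controls are judged six months later, when some have remitted. Control losses therefore include people who recovered, while early-arm losses are only those never confirmed at the start.

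At stake is a primary objective: the remaining controls are those who did less well, so early treatment can appear effective when it is not.

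**Working it through.** **Plan figures.** The sample size section states "resulted in a required group size of 48 patients per diagnostic group (24 TAU+SI-T0 and 24 TAU+SI-T1"), and 46 per arm for depression and PTSD. Per arm: 2 × 46 + 6 × 24 = 236. Both arms: 472, matching "a total of 472 participants will be included in this study". The article gives no figure for the share excluded or its effect.

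**Assumptions.** Normally distributed scores, no true effect, and a fraction p of controls with the lowest T1 HSDQ removed. I use p = 10% and 20%, and a correlation r = 0.5 between HSDQ and another outcome. None of these comes from the article.

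**Rule 1, level at T1.** The mean of the remaining controls rises by λ = φ(z_p)/(1 − p):

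- p = 10%: 0.1755/0.90 = 0.195 SD
- p = 20%: 0.280/0.80 = 0.350 SD
- Wider range: 5% gives 0.109 SD, 30% gives 0.497 SD.

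For another outcome the shift is r × λ: 0.5 × 0.195 = 0.097 and 0.5 × 0.350 = 0.175 SD.

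**Rule 1, change from T0.** A null simulation with entry only above the cut-off and a T0-T1 correlation of 0.6 gives 0.13 SD (10% removed) and 0.23 SD (19% removed). This is smaller than the shift in level, because the removed controls also started somewhat lower.

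**False-positive rate, r = 0.5, two-sided 5%.** The remaining controls' HSDQ variance is v = 1 + z_p λ − λ², which is 0.712 (10%) or 0.583 (20%). For the correlated outcome it is 1 − r²(1 − v), which is 0.928 or 0.896. SE = √[1/n + variance/(n(1 − p))], and the rate is Φ(shift/SE − 1.96) + Φ(−shift/SE − 1.96).

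| n per arm | Removed | Shift (SD) | SE | Rate |
|---|---|---|---|---|
| 236 | 10% | 0.097 | 0.0928 | 18% |
| 236 | 20% | 0.175 | 0.0948 | 46% |
| 24 | 10% | 0.097 | 0.291 | 6% |
| 24 | 20% | 0.175 | 0.297 | 9% |

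A direct simulation gives 19% and 46% at 236 per arm, and 6% and 9% at 24 per arm. For T1 HSDQ itself at 236 per arm, the formula gives 61% and 98%.

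**Rule 2.** In the same simulation, with a noisy confirmation step, the settings in which rule 1 removes 10% and 19% of controls have rule 2 removing 7% and 11% of the early arm at T0, against 13% and 22% of controls at T1. The net shift in change is 0.17 and 0.26 SD toward early treatment. Both rules together give 0.20 and 0.32 SD at T1, and 0.07 and 0.11 SD at T2.

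**If only T1-T2 follow-up is lost under rule 1.** The T1 data remain, so the six-month comparison is untouched. At 12 months, missing T2 depends on a T1 HSDQ score that was observed. Complete cases would shift T2 HSDQ by 0.6 × λ, that is 0.12 and 0.21 SD. A likelihood-based model that includes the T1 score brings the bias to about zero in simulation. A model for another outcome does not contain that score, so bias remains wherever T1 HSDQ predicts the 12-month value beyond what that outcome's own T0 and T1 values predict.

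**The case against.** **Removal from the analysis is inferred.** The Procedure section says outright that very severe controls leave the analysis of treatment effects. The two rules here refer instead to the treatment part of the study, and the wording of rule 1 ties this to eligibility for treatment. The paragraph just before keeps participants without T2 in comparisons of T0 with T1, and a control caught by rule 1 has both. This stands as a real ambiguity. Against it, the sentence sits under Statistical analyses, the effect analysis is confined to participants with a sleep disorder, and no sentence keeps these people in the comparison.

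**The size can be overstated.** A reader might set the 0.35 SD shift in HSDQ against the target and conclude that it amounts to nearly the whole planned effect. The documents do not support that: where they say "we aim at an effect size of 0.4", they mean quality of life, general functioning and disorder-specific symptoms, not HSDQ. The comparable shift is 0.10-0.18 SD. The high false-positive rates need the full 236 per arm, while disorder-specific outcomes are mostly analysed at 24 per arm. Entry is by any HSDQ category, so falling below every cut-off is not a sharp truncation of the total score, and the true shift would be somewhat smaller.

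**Not everything pulls one way.** Rule 2 also removes early-arm cases. Dropping very severe controls lowers the control mean in raw levels, although in change from T0 it added about 0.02-0.04 SD toward early treatment when the top 2-5% were removed.

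These points limit the certainty and the size. They do not remove the asymmetry in rule 1.

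**Conclusion.** The concern holds in a bounded form. On the most natural reading, rule 1 removes controls because of a good outcome, in one arm only, and its direction is clear: it favours early treatment. Rule 2 probably adds to this, less certainly.

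With 10-20% of controls removed and no true effect, rule 1 shifts T1 HSDQ by about 0.20-0.35 SD, or 0.13-0.23 SD in change from T0. Outcomes correlated 0.5 with HSDQ shift by about 0.10-0.18 SD, roughly a quarter to under a half of the d = 0.4 set for them (0.097/0.4 = 24%; 0.175/0.4 = 44%). The removal share and the correlation are assumptions, and the false-positive rate is a serious problem mainly for the whole-sample analyses.

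A reader might also infer that the 12-month comparison is biased on any reading. That goes too far. If only T1-T2 follow-up is lost, the six-month result is intact and a mixed model for HSDQ largely handles the rule 1 selection; only 12-month results for outcomes modelled without HSDQ may remain biased. That the readings lead to different results is itself reason to rewrite the paragraph.

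**What to change.** 1. State that all randomised participants receive the T1 and T2 questionnaires and are analysed in their assigned arm, whatever their T1 HSDQ score or diagnostic result. The decision on offering sleep treatment stays as the article describes it.
2. Apply the same analysis rule to the control-only exclusion of very severe cases in the Procedure section. Alternatively, define that exclusion from data collected before randomisation and apply it alike in both arms.
3. Report any analysis that uses these exclusions, or a confirmed-disorder subset, only as a sensitivity analysis, labelled as subject to diagnostic timing that differs by arm. Without that label it would bring back the same selection.

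The cost is a few sentences of analysis wording and T2 questionnaires for people already enrolled on the existing online platform. The downside is that unconfirmed cases, and very severe controls treated early, dilute the estimated effect somewhat.

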#### Prevalence

Descriptive statistics will be used to assess the prevalence of the different sleep disorders over the entire study population and within different subgroups of mental disorders. The prevalence of the six different types of sleep disorders (based on the HSDQ indicated diagnosis) will be calculated as a frequency for the total study population and for the eight mental disorder diagnostic groups separately. Differences in prevalence between the various mental disorder diagnostic groups will be computed using chi-square and/or Phi or Cramer-V analysis. The Standardized incidence ratio (SIR) will be calculated for the clinical population relative to reported prevalence of the different sleep disorders in the general population.

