### Study outcomes

Primary outcomes are 1) the prevalence of different sleep disorders as a function of individuals’ mental disorders (depressive disorder, bipolar disorder, anxiety disorder, PTSD, AD(H)D, ASD, SSD or personality disorder), and 2) the effect of sleep interventions on sleep, severity of specific symptoms of mental disorders, general functioning, and quality of life. Secondary outcomes are 1) the effects of sleep interventions on objective outcome parameters, for example use of sleep/sedative medication, number of hospitalizations and length of stay and, 2) differences between genders in the prevalence of specific sleep disorders and sleep intervention effects.

First, we expect that the prevalence of most sleep disorders among individuals with mental disorders will exceed those in the general population. Second, concerning the adjusted sleep interventions, we expect that the treatment of sleep disorders, tailored to mental disorders, will improve sleep, recovery from mental disorder symptoms, and quality of life in most patients. We hypothesize that the effect of added sleep intervention(s) will be larger than the effect of TAU alone in the TAU-SI-T1 group.

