### Sleep disorder diagnosis

The sleep diagnostic process depends on the suspected sleep disorder(s) indicated by the HSDQ. Each participant scoring positive for one or more (types of) sleep disorder(s) will be invited for a sleep diagnostic interview by trained psychologists. Participants will also be asked to complete one or more short questionnaires (5–10 min) during this interview, depending on the HSDQ-indicated sleep disorder(s). The following questionnaires will be used: the *Pittsburgh Sleep Quality Index* (PSQI) [40] for subjective quality of sleep; *Insomnia Severity Index* (ISI) [41] in participants with HSDQ-indicated Insomnia disorder; *Morningness - Eveningness Questionnaire* [42] in participants with HSDQ-indicated CRSD; *Epworth Sleepiness Scale* (ESS) [43] in participants with HSDQ-indicated SRBD and/or hypersomnia and; *International RLS study group rating scale* (IRLS) [44] in patients with HSDQ-indicated RLS. An additional file is added, and describes the sleep-oriented questionnaires in more detail (see Additional file 1). In order to evaluate the effect of sleep disorder treatment, the same questionnaires will also be filled out by the participants directly following the sleep intervention.

The diagnostic interview takes around 30–60 min. Hereafter, participants will be asked to wear an actigraph (Motionwatch 8, CamNtech) for two weeks in case of CRSD, and for one week in all other cases. This actigraph is a diagnostic instrument in the form of a wristband that registers bodily activity in order to asses objective sleep quality and sleep-wake pattern. Additionally, participants will be asked to complete a sleep diary for the same time period they wear the actigraph, in which they note their bedtimes, estimated sleep latency, total sleep duration, sleep quality, and number of awakenings. If further information is needed for diagnosis, additional diagnostic measurements will be made, such as polysomnography, Dim Light Melatonin Onset (DLMO) measurement to determine the circadian rhythm in CRSD and Multiple Sleep Latency Test (MSLT) to evaluate hypersomnia. For diagnosing sleep disorders, ICSD-3 criteria [4] will be followed. Final diagnosis will be made during a multidisciplinary consultation with a somnologist, a somno-technologist and psychologists. Complex cases will additionally be discussed with a neurologist, pulmonary-specialist, and/or psychiatrist.

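### Primary-outcome prevalence counts HSDQ screen-positives and is divided by general-population figures of unstated definition, under the name of an incidence ratio, so false positives can produce the hypothesised excess

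*Protocol article*

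**What the plan says.** All passages are in the protocol article.

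- **Status of the estimate.** Study outcomes: "Primary outcomes are 1) the prevalence of different sleep disorders as a function of individuals’ mental disorders". The attached hypothesis is that "we expect that the prevalence of most sleep disorders among individuals with mental disorders will exceed those in the general population".
- **Case definition.** The Sleep subsection of the measures says that "the HSDQ will be used for screening purposes and to assess sleep disorder prevalences". The Prevalence section repeats this: "The prevalence of the six different types of sleep disorders (based on the HSDQ indicated diagnosis) will be calculated as a frequency".
- **External comparison.** Prevalence section: "The Standardized incidence ratio (SIR) will be calculated for the clinical population relative to reported prevalence of the different sleep disorders in the general population". It does not say how cases were defined in those reported figures.
- **Clinical diagnosis.** HSDQ-positive participants are worked up and diagnosed at a multidisciplinary consultation. Sleep disorder diagnosis: "For diagnosing sleep disorders, ICSD-3 criteria [4] will be followed". The HSDQ itself is described as based on ICSD-2.
- **Unconfirmed positives.** Data exploration/ missing data names a scenario in which "a participant scores above a cut-off score of the HSDQ, but that the sleep disorder is not confirmed in the diagnostic evaluation". Such a participant leaves the treatment part. Nothing removes that participant from the prevalence count.

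**The concern.** The numerator of the ratio is a questionnaire screening rate. The denominator is whatever prevalence has been published, possibly under another definition. When a condition is uncommon, even a small false-positive rate among the many unaffected people can outnumber the cases that the screen misses, and the apparent prevalence then exceeds the true one. The hypothesis asks only whether prevalence exceeds the general-population figure, so any upward shift pushes towards confirming it.

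The plan has the means to see the problem, since the ICSD-3 consultation shows how many positives are confirmed, but it does not bring that result into the prevalence aim.

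The label adds to the difficulty. A ratio of cross-sectional prevalences is not an incidence ratio, and no standardisation is described.

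What is at stake is stated in the Discussion: a high observed prevalence may steer resources to a particular sleep disorder and suggest aetiological pathways.

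**Working it through.** The plan gives no expected prevalence, ratio, sensitivity or specificity for this analysis, so there is no figure of its own to reproduce. The check asks what the planned ratio would show if the clinical population had exactly the general-population prevalence.

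**Inputs**
- True prevalence p = 0.06: the Background figure for chronic insomnia, and the only general-population prevalence in the document. It is used as an example; the plan does not name it as the reference.
- HSDQ accuracy: the Sleep subsection gives an area under the curve of .95 (total score, diagnosed patients against people without sleep complaints) and kappa = .80. Neither refers to the six category cut-offs.
- Sensitivity (Se) and specificity (Sp) per category: not given, so assumed and varied. One anchor is that kappa .80 corresponds to Se = Sp = 0.90 at an assumed 50:50 mix.

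**Formulas**
- Apparent prevalence = p × Se + (1 − p) × (1 − Sp)
- Ratio = apparent prevalence / p
- Positive predictive value (PPV) = p × Se / apparent prevalence

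**Results at p = 0.06, no true excess**

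| Se / Sp | Apparent prevalence | Ratio | PPV |
|---|---|---|---|
| 0.80 / 0.85 | 0.048 + 0.141 = 0.189 | 3.15 | 25% |
| 0.90 / 0.90 | 0.054 + 0.094 = 0.148 | 2.47 | 36% |
| 0.85 / 0.95 | 0.051 + 0.047 = 0.098 | 1.63 | 52% |
| 0.90 / 0.99 | 0.054 + 0.0094 = 0.0634 | 1.06 | 85% |
| 0.70 / 0.99 | 0.042 + 0.0094 = 0.0514 | 0.86 | 82% |

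**Break-even.** The ratio exceeds 1 when 1 − Sp > (1 − Se) × p / (1 − p). At p = 0.06 the break-even specificity is 1 − 0.10 × 0.06/0.94 = 0.994 for Se 0.90, 0.981 for Se 0.70 and 0.968 for Se 0.50. Below these values there is a spurious excess; above them the bias reverses.

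**Rarer disorders.** With prevalence assumed and Se = Sp = 0.90, the apparent figure at 3% is 0.027 + 0.097 = 0.124 (ratio 4.1), and at 1% it is 0.009 + 0.099 = 0.108 (ratio 10.8). This gradient depends on specificity being the same in each category.

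**Confirmed cases only.** In the 0.90/0.90 scenario, counting only screen-positives that a perfect work-up confirms gives 0.90 × 0.06 = 5.4%, a ratio of 0.90. The apparent excess disappears, and the small shortfall is the cases that the screen missed.

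**The case against.** Several counter-arguments have force.

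- **The size is not established.** This stands. The accuracy figures are for the total score or the whole instrument, and each category has its own cut-off. The credible range runs from below 1 to above 3.
- **The reference sources may be matched.** The article does not name them, and their choice is the kind of detail left to a fuller document. If they were HSDQ-based, misclassification would partly cancel. This limits the point to what false positives can do. It does not remove it, because the case definition and the ratio are fixed in the text with no requirement that definitions match.
- **The definition is disclosed, and the comparison across mental disorders uses one instrument.** True, and the HSDQ rate remains reportable. The hypothesis about the general population, however, rests on the external contrast.

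A reader might also infer more than the documents support:

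- That the plan expects many unconfirmed positives. It names the scenario and gives no frequency.
- That the bias must be largest for the rarer disorders. This needs equal specificity across categories, which nothing shows.
- That overlap between psychiatric symptoms and HSDQ items does distort comparisons between diagnostic groups. It could, but the document offers no evidence either way.
- That the immediate-treatment arm is a random half of all HSDQ-positives. Under Procedure and Sample size calculations, positives are invited, give consent and are only then randomised, towards targets per diagnosis of 48 or 92. The arm is a random half of consenting, quota-enrolled positives.

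**Conclusion.** The concern holds as a mismatch of case definitions and a wrong label in the analysis of a primary outcome. Following the plan as written, an excess over the general population can appear when none exists, because unconfirmed screen-positives still count as cases and the reference need not share their definition.

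The illustrative ratios at a true prevalence of 6% (0.86 to 3.15) rest on assumed sensitivity and specificity and on the Background insomnia figure. They show the possible direction and scale and do not estimate the bias in this trial.

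The documents do not support concluding that any excess found would be spurious. Of the scenarios in the table, none reaches the contrast in the Background between more than 40% in schizophrenia spectrum disorders and about 6% in the general population (40/6 = 6.7), and one reverses the bias.

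**What to change.** 1. **Rename the estimate.** Report the HSDQ figure as an HSDQ screen-positive rate.
2. **Replace the SIR.** Use an age- and sex-standardised prevalence ratio, computed only against reference rates of the same definition: HSDQ or a comparable questionnaire against HSDQ, diagnosed against confirmed. Where no matched reference exists, do not conclude that prevalence exceeds that of the general population.
3. **Add a supportive confirmed-prevalence estimate.** For each sleep disorder category, pooled over diagnostic groups, multiply the screen-positive rate by the PPV from ICSD-3 diagnoses in TAU+SI-T0, the arm evaluated at T0. Reweight to the diagnostic mix of all screened patients, because the enrolment targets change that mix, and give a bootstrap interval.
4. **State its limits.** It assumes equal PPV in consenting and non-consenting positives. HSDQ-negatives are not evaluated, so it is a lower bound only if that assumption holds. Estimates within single diagnostic groups are descriptive: six of the eight have 24 patients in the arm. If half of those were positive for a category (assumption), a PPV of 6/12 would have a 95% Wilson interval of about 0.25 to 0.75.

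The ICSD-3 work-up is already planned, so the cost is a little more analysis, plus confirmed figures that are lower and less precise than the HSDQ rates.
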